## Methods

### Study design

A two-arm randomized controlled trial was designed to identify the effect of a new EBF counselling intervention specifically designed to support overweight women, on the prevalence of breastfeeding and EBF, infant growth velocity and maternal postpartum weight loss up to 4 months. Although the primary end-point will be 4 months after delivery, mothers will be advised to continue EBF until 6 months, as recommended by WHO.

The trial involves overweight women recruited in the last month of pregnancy and their infants. Eligible overweight women will be randomly assigned to an intervention or control group and outcomes will be measured from birth and up to 4 months after delivery. The control group will receive standard counselling from Baby Friendly Hospitals, while the intervention group will receive the new EBF counselling intervention for overweight women. The intervention will be carried out at three time-points:
i)Last month of pregnancy.ii)24 h postpartum.iii)Early infancy (1 and 3 months postpartum).

### Hypotheses and outcome variables

#### Primary hypotheses

Compared to standard management, the implementation of a new EBF counselling intervention for overweight woman will result in:
i)an increase in the prevalence of breastfeeding and EBF from birth up to four months of age;ii)slower infant weight for length growth from birth up to four months of age;iii)an increase in weight loss after delivery up to four months postpartum.

#### Primary outcomes and variables

Outcomes will be measured at birth (baseline) and 1, 3 and 4 months postpartum in the intervention and control groups. The primary outcomes are:
i)Prevalence of breastfeeding and EBF, ascertained by asking the mother about infant feeding practices during the last 24 h;ii)Growth velocity from birth, defined as change in weight for length in g/cm and length for age in cm/days;iii)Maternal weight loss after delivery in kg, using maternal weight at 24 h as baseline.

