#### Essential time-points for intervention

Three key time-points to intervene were identified to increase the duration of EBF in overweight women, according to their particular needs [63]: i) the last month of gestation as the moment to identify mechanical problems such as larger breasts and flattened nipples [64] and the intentions and fears of the women regarding breastfeeding [65], to promote the importance of early contact (skin to skin) between the women-infant dyad [66] and initiation of breastfeeding in the first hour postpartum [67], and to prepare the women to recognize adequate infant latch-on; ii) 24 h postpartum to evaluate suckling, early initiation of breastfeeding and beginning of lactogenesis II [68]; iii) early infancy (1 and 3 months postpartum) to empower the women in the continuation of EBF (periods where there is a risk of early weaning) [69]. During each counselling session, counselling support materials with key messages will be given to the women to reinforce counselling. Counselling will be evaluated at every time-point using a structured questionnaire about maternal satisfaction and usefulness. Adherence to EBF will be assessed by asking the mother if she has exclusively breastfed during the last 24 h at each time-point.

Women with breastfeeding difficulties at the time of the intervention that are beyond the scope of the researcher’s competence will be referred to the relevant professional so that appropriate treatment can be offered to promote continued breastfeeding (e.g. physician, nurse, psychologist). Referrals and the reason for the consultation will be recorded and compared between groups.

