#### Measures

Questionnaires and assessments will be used to collect information among intervention and control groups at specific time-points, as shown in Table 1.
Maternal socioeconomic and demographic information, pregnancy information and paternal information: Information about residency, age, marital status, occupation, socioeconomic level, family size, family income, educational level, maternity leave, access to public services, social security, health benefits, smoking, alcohol consumption, family and medical history will be recorded. Gestational age will be determined by the date of the last menstruation, corroborated by sonographic studies available in the clinical notes. Paternal information will be reported by the woman and will include health status and monthly income.Intention to breastfeed: The scale uses five simple questions to determine the method of feeding that the woman plans for the baby. The scale has been validated and translated in previous studies [60].Maternal anthropometry: Anthropometric data - weight, height and mid upper arm circumference (MUAC) - will be collected in the last month of pregnancy, 24 h postpartum, and 1, 3 and 4 h months postpartum in minimal clothes. Weight will be measured in duplicate using an electronic scale (SECA 813, capacity 200 kg, precision 100 g), height measured in triplicate using a portable stadiometer (SECA 213, up to 205 cm) and MUAC measured in triplicate to the nearest cm (SECA 203 measuring tape, range 0 to 205 cm, graduation 1 mm). Weight gain during gestation (self-reported weight at the end of gestation minus pre-gestational weight) will be used as a baseline characteristic and as a covariate to predict the main outcomes.Breast examination: Participants will complete a questionnaire using illustrations of breasts to identify possible anatomical aspects that could make breastfeeding difficult (e.g. large breasts, flat nipples). This information will be used to focus the intervention for individual mothers.Edinburgh Postnatal Depression Scale (EPDS): This consists of 10 questions about feelings during the last week. It will be administered during the last month of gestation and 1 month postpartum as a tool to determine the risk of postpartum depression [54].Counselling register and evaluation: To assess the content of and adherence to the new EBF counselling intervention, a record of the problems identified will be kept during each visit. A questionnaire will also be administered by an independent investigator blinded to group allocation at the end of the study period (four months postpartum) which will include information on the problems identified, solutions and success, measured as: not successful (no problem resolution); limited success (partial resolution of the problem), or successful (problem solved).IPAQ short version: Physical activity questionnaire which considers types of physical activity, time (minutes per day) and number of days per week, and number of hours per day that the woman remains seated [61].Maternal food consumption: Determined using a standard food frequency questionnaire used and adapted in Colombian populations in other studies, and two multiple steps 24-h recall questionnaires to determine food consumption and nutrient intake including supplements, vitamins, minerals and maternal feeding problems; to be used as a baseline descriptive characteristic and as a potential confounder. This methodology is based on that described by the United States Department of Agriculture [58, 59]. To improve the quality of the data, photographs will be used to determine portion size [70]. Data analysis will be conducted using Colombian food composition tables [71], USDA standard nutrient reference database and food labels.Delivery information: Data about the type of delivery, newborn APGAR score, time of breastfeedng initiation, maternal-infant complications including those which delay the initiation of breastfeeding, and drugs administered during labour and the first 4 months after delivery.Newborn and infant anthropometry: Anthropometric variables - weight, length, MUAC and head circumference - will be measured by a trained nutritionist and dietitian following WHO protocol [72] at birth and 1, 3 and 4 months postpartum. Infant weight will be measured in duplicate using an electronic baby scale (TANITA 1583 with precision of 10 g, capacity 200 kg), length measured in triplicate using an infantometer (SECA 417, folding mechanism and foot stop, measuring range up to 100 cm), and head circumference and MUAC measured using a pediatric tape measure (SECA 201, range 0 to 205 cm, graduation 1 mm). Infant growth velocity will be defined as the change in the Z-score of weight for length, length for age, head circumference for age and mid upper arm circumference for age from birth to four months according to WHO growth standards [73]. Data collection will be performed by the same researcher in both groups to control information bias among observers.Breastfeeding information: This questionnaire collects information about initiation of breastfeeding at the hospital.Infant 24-h dietary recall: To determine the EBF prevalence, an infant 24-h recall will be used asking mothers about the foods consumed by the child during the previous day and infant feeding practices at 1, 3 and 4 months. = The counsellor will ask about the initiation, frequency and mode of preparation of specific beverages and semisolid foods or supplements since the last visit. This methodology will allow breastfeeding to be classified as exclusive or predominant according to WHO definitions [12].Breast-latching observation: Considers information about position of breastfeeding and maternal-infant perception of comfort during breastfeeding. This is a check-list that the investigator completes after watching a breastfeed [74].Breast milk macronutrients: Expression of breast milk (fore milk) will be performed at 1 and 4 months postpartum at the researcher’s office in the morning, using a Philips Single Electric Breast Pump under researcher supervision. The sample will be stored at − 20 °C in the laboratory at the Pontificia Universidad Javeriana for analysis. Content of macronutrients (carbohydrate, protein and fat) and energy in breast milk will be determined using the MIRIS Human Milk Analyzer, which uses infrared transmission spectroscopy and requires a human milk sample of 5 ml. Results will be recorded in the database.Breast milk prolactin: Determination of breast milk prolactin concentration will be performed using an Abcam ab226901 Human Prolactin SimpleStep ELISA kit. The procedure requires 2 ml of breast milk.Serum prolactin: To determine the maternal serum prolactin concentration, a non-probabilistic convenience subsample of 60 (20%) women will be selected. The blood sample will be taken at the laboratory of the institution, within 2 h of waking in the morning and before any food is consumed. The procedure will require 5 ml of maternal blood, which will be analyzed by ELISA (Abcam ab226901).

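### The primary outcome infant growth velocity is defined in two incompatible ways, with no rule for which one counts

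*Protocol article*

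**What the plan says.** Primary outcomes and variables lists growth velocity second among three primary outcomes: "Growth velocity from birth, defined as change in weight for length in g/cm and length for age in cm/days".

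Measures, under newborn and infant anthropometry, defines the same outcome again: "Infant growth velocity will be defined as the change in the Z-score of weight for length, length for age, head circumference for age and mid"-upper "arm circumference for age from birth to four months according to WHO growth standards".

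Primary hypotheses gives a direction for only one index and no unit: "slower infant weight for length growth from birth up to four months of age". Statistical analysis refers to infant growth velocity by name and adds no definition. Study design names 4 months after delivery as the primary end-point.

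For EBF, the primary outcome is "Prevalence of breastfeeding and EBF, ascertained by asking the mother about infant feeding practices during the last 24 h". Measures also uses an infant 24-h recall to determine EBF prevalence, but adds: "The counsellor will ask about the initiation, frequency and mode of preparation of specific beverages and semisolid foods or supplements since the last visit". It then says that this methodology classifies feeding as exclusive or predominant.

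**The concern.** Both growth passages are worded as definitions of the same primary outcome, and they do not describe the same quantity. One is in raw units and the other is standardised to the WHO reference. One has two components and the other has four. An analyst who follows the document faithfully can report a raw weight-for-length result, a Z-score weight-for-length result, or one of the other indices, and call any of them the primary growth result.

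The choice matters because the trial intends to draw a conclusion about growth. Randomization and masking says that the researcher who delivers the intervention and collects the data cannot be blinded, which adds to the value of fixing the variable in advance.

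The EBF wording raises a smaller question of the same kind: whether the longer feeding history is meant to enter the classification.

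**Working it through.** **1. The two growth definitions side by side**

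| Feature | Primary outcomes and variables | Measures |
|---|---|---|
| Scale | Raw: g/cm and cm/days | Change in WHO Z-score |
| Weight for length | Yes | Yes |
| Length for age | Yes | Yes |
| Head circumference for age | No | Yes |
| MUAC for age | No | Yes |
| Period | From birth, end not stated | Birth to four months |
| Number of measures | 2 | 4 |

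The period can be reconciled, since Primary hypotheses and Study design both point to four months. Scale and number of measures cannot.

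**2. The raw unit has two readings**

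Assumed infant (not from the document): 3,200 g and 49 cm at birth, 6,400 g and 62 cm at four months.

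- Weight gained per cm gained: (6400 − 3200)/(62 − 49) = 3200/13 = 246 g/cm.
- Change in weight/length ratio: 6400/62 − 3200/49 = 103.2 − 65.3 = 37.9, or about 38 g/cm.

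The two readings are not rescalings of each other. With W for weight, L for length, 0 for birth and 1 for four months:

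W1/L1 − W0/L0 = (ΔL/L1) × (ΔW/ΔL − W0/L0).

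Check: (13/62) × (246.2 − 65.3) = 37.9. The second reading therefore also depends on how much length was gained. Two infants with the same size at birth and the same gain per cm can differ on it.

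For weight for length alone, the one index in the primary hypothesis, the text supports three candidate variables: two raw readings and one Z-score change. With raw length for age and the other three Z-scores, the count is seven.

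**3. What a free choice could cost (illustration)**

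Two versions of one endpoint are each tested at two-sided 5%, there is no true effect, and the better one is reported.

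- Independent: 1 − 0.95² = 9.75%.
- Correlated, from one million simulated pairs of normal test statistics:

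| Assumed correlation | False-positive rate |
|---|---|
| 0.70 | 8.4% |
| 0.80 | 7.8% |
| 0.90 | 7.0% |
| 0.95 | 6.5% |

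The document gives no correlation, so these values only show a range.

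**4. Does the sample size depend on the growth definition?**

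Inputs from Sample size: control EBF 22.8%, difference 23 points (taken as 22.8% against 45.8%), power 95%, two-sided 5%, losses 20%.

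n per arm = [1.960 × √(2 × 0.343 × 0.657) + 1.645 × √(0.228 × 0.772 + 0.458 × 0.542)]² / 0.23² = 108, or 117 with continuity correction. Then 117/0.80 = 147 per arm, against the stated 145. The stated figure is reproduced to within 2 per arm, and no growth quantity enters it.

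**5. EBF**

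The 24-h window appears in the primary outcome, in the adherence statement ("Adherence to EBF will be assessed by asking the mother if she has exclusively breastfed during the last 24 h at each time-point"), in the infant 24-h recall rows of Table 1 and in the instrument described under Measures. The since-last-visit questions sit within that instrument, and no section makes them an endpoint. The only loose end is that Measures does not say they stay out of the classification. If they did enter it, EBF prevalence could only fall or stay the same.

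**The case against.** **A statistical analysis plan may settle the growth variable.** One may exist and is not shown, so selection after seeing the data is an opportunity, not something that the document states. That is fair. But an analysis plan that chose either version would still contradict one of the two sections.

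**The g/cm example shows no effect on the treatment comparison.** This stands. It shows that the unit is ambiguous for one assumed infant. It does not compare raw units with Z-scores, and it does not show that the difference between arms would change. Standardisation for sex is likewise a weak argument in a randomised comparison, where sex is balanced in expectation.

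**The outcomes section could simply govern, with Z-scores secondary.** That would also remove the contradiction, and the secondary hypotheses do mention WHO growth standards. It would still need the g/cm unit to be defined.

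**Stronger readings to avoid.** A reader might infer that EBF has two competing primary definitions and that power is therefore at risk. The document does not support this. It ties EBF to the last 24 h throughout, and any power loss would need an endpoint it does not state plus assumed rates of earlier supplementation. A reader might also infer that the primary endpoints as a whole are not fixed. That is too broad: maternal weight loss has one definition (kg, from the 24 h weight), and 4 months is named as the primary end-point.

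**Conclusion.** The contradiction over infant growth velocity is real and rests on the text alone. The two definitions differ in scale and in number of measures, one of the units is ambiguous, and nothing in the document ranks them. The trial cannot state a single primary growth result until this is settled.

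The practical size cannot be derived from the document. The 6.5% to 9.75% range shows the inflation from choosing between two versions, under the correlations assumed above. It is not an estimate for this trial. The planned 290 dyads and the EBF comparison are untouched. The EBF wording needs a minor clarification only.

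**What to change.** 1. State one primary growth variable, scale and period, identically in Primary outcomes and variables and in Measures. Change in WHO weight-for-length Z-score from birth to 4 months is a good candidate: it matches the index in the primary hypothesis and avoids the ambiguous g/cm unit.
2. Label length for age, head circumference, MUAC and any raw-unit measure as secondary or descriptive. If a g/cm measure is kept, give its formula.
3. Add one sentence to the infant 24-h recall text under Measures: last-24-h status decides the EBF classification, as the primary outcome already says, and the since-last-visit history does not enter it. That history may serve a sensitivity analysis.

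The cost is wording only. The weights, lengths, circumferences and feeding histories are already planned, and no visit, measurement or participant is added. The change should be made, and dated, before the growth data are compared between arms.

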#### Secondary hypotheses

Compared to standard management, the implementation of a new EBF counselling intervention designed to support overweight woman will result in:
i)An increase in the volume of breast milk in ml as a result of an increase in serum prolactin levels in ng/ml, at 1 and 4 months.ii)Higher milk prolactin concentration and adequate macronutrient content of protein, lactose, fat and energy, at 1 and 4 months, which will in turn be associated with more optimal infant growth (based on WHO growth standards).

### Secondary outcomes and variables

i)Maternal serum levels of prolactin and breast milk prolactin concentration and macronutrient content, measured at 1 and 4 months after delivery;ii)Estimated breast milk intake at 1 and 4 months according to WHO recommendations [53].

The study design is shown in Fig. 1 and a timeline of measurements in Fig. 2.

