### Sample size

The sample size was calculated to detect a difference in the prevalence of EBF between the intervention and control group of 23%, based on literature [43] reporting a baseline EBF of 22.8% in the control group (the prevalence of EBF for the Colombian population at 4 months in urban areas in 2010 [55]; there is a lack of data on EBF prevalence in overweight women in Colombia), with a power of 95%, an alpha error of 5% and a two-tailed calculation determined using the EpiInfo StatCalc program [56]. Assuming follow-up losses of 20%, 290 woman-child dyads are required, 145 in each group.

A convenience subsample of 60 women will be recruited, 30 from each group (20% of overall sample) for analysis of serum and milk prolactin concentration and macronutrient content.

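### Milk prolactin and milk macronutrients can be measured only in women still lactating, a state the counselling is meant to change, so their between-arm comparison is not a randomised one

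*Protocol article*

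**What the plan says.** All references are to the Methods of the protocol article unless stated.

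- **Primary hypotheses.** Compared with standard management, counselling will raise the prevalence both of any breastfeeding and of exclusive breastfeeding (EBF), from birth to 4 months.
- **Secondary hypotheses.** These are also framed against standard management. The first concerns volume: "An increase in the volume of breast milk in ml as a result of an increase in serum prolactin levels in ng/ml, at 1 and" 4 months. The second states that milk prolactin will be higher and milk macronutrients adequate at 1 and 4 months, and links both to infant growth.
- **Secondary outcomes and variables.** The laboratory outcomes are "Maternal serum levels of prolactin and breast milk prolactin concentration and macronutrient content, measured at 1 and 4 months after delivery". Estimated milk intake is a separate item.
- **Measures.** Macronutrients and milk prolactin are assayed in breast milk, and the pumped sample is scheduled at 1 and 4 months. Serum prolactin comes from a blood sample.
- **Table 1, and Strengths and limitations.** Milk intake is estimated by an algorithm. The number and length of feeds are recorded at each postpartum visit.
- **Sample size.** Milk and serum assays are done in a convenience subsample of 60 women, 30 per arm.
- **Statistical analysis.** Intention to treat is stated for the main analysis. Nothing is said about women who have no milk to sample.

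**The concern.** The two milk-concentration outcomes have no value in a woman who has stopped lactating. Whether she has stopped is settled after randomisation, and the trial's own primary hypothesis says the arms will differ on it. If counselling works, the women giving milk in the intervention arm include some whose counterparts in the control arm have weaned. The two sampled groups are then not alike, even if the women originally chosen for sampling were.

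At stake is the proposed mechanism. The second secondary hypothesis runs from counselling, through milk prolactin and composition, to infant growth. A between-arm difference in milk concentration could reflect who is still lactating and not what counselling did to the milk, and a real difference could be hidden in the same way. A larger sample would not remove this.

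**Working it through.** **1. The plan's own calculated figure.** The only sample size derived is for EBF: "a difference in the prevalence of EBF between the intervention and control group of 23" percentage points, "reporting a baseline EBF of 22.8% in the control group", "with a power of 95%, an alpha error of 5% and a two-tailed calculation". Comparing 22.8% with 45.8%, with continuity correction, gives 117 per arm. Allowing for 20% loss, 117/0.80 = 146.25, so 147 per arm. The protocol states: "Assuming follow-up losses of 20%, 290 woman-child dyads are required, 145 in each group". The figure reproduces to within 2 per arm and is not in dispute. No calculation is given for the milk outcomes.

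**2. The passages side by side.**

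| Element | Where | Consequence |
|---|---|---|
| Counselling raises any breastfeeding to 4 months | Primary hypotheses | Lactation status is affected by treatment |
| Milk prolactin and macronutrients are measured in breast milk | Measures | No value after weaning |
| Both are claimed to be better than under standard management | Secondary hypotheses | A causal between-arm claim |
| Intention to treat for the main analysis | Statistical analysis | Cannot create the absent values |

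The first two rows mean that the third cannot be tested by comparing the arms as randomised.

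**3. How large might the bias be?** The document gives no rate of any breastfeeding by arm, so every rate below is an assumption. Both models assume no true effect on milk. Both also assume that women who continue only because of counselling have lower values.

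*Model A: simple mixture.* Let p be the share lactating in the control arm, e the extra share retained by counselling, and d the deficit of the retained women in SD. The intervention mean is shifted by

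bias = -d × e/(p + e).

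With p = 0.70 and d = 1:
- e = 0.05: -0.05/0.75 = -0.07 SD
- e = 0.15: -0.15/0.85 = -0.18 SD
- e = 0.25: -0.25/0.95 = -0.26 SD

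*Model B: correlated propensity.* Let ρ be the correlation between the tendency to keep lactating and the milk value. Among women lactating, the mean is ρφ(c)/p, where c is the normal quantile at 1 - p. For 70% versus 80% lactating, φ(c)/p is 0.497 and 0.350. The difference is -0.147ρ, which is -0.04 SD at ρ = 0.3 and -0.10 SD at ρ = 0.7. Across assumed rates:

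| Lactating, control vs intervention | ρ = 0.3 | ρ = 0.7 |
|---|---|---|
| 95% vs 98% | -0.02 | -0.04 |
| 70% vs 80% | -0.04 | -0.10 |
| 60% vs 83% | -0.10 | -0.24 |

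Together the two models span about -0.02 to -0.26 SD. If the retained women had higher values (d or ρ negative), every sign would reverse.

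**4. Scale.** With 30 per arm, the difference detectable at 80% power is (1.960 + 0.842) × √(2/30) = 0.72 SD. With 24 per arm after 20% loss it is 0.81 SD. At 70% versus 80% lactating, only 21 and 24 of 30 women could give milk, before other losses.

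**5. Sampling time.** Table 1 places milk macronutrients and serum prolactin at 1 and 3 months and lists neither at 4 months. The Secondary outcomes section places all the laboratory outcomes at 1 and 4 months, and Data collection and Measures do the same for milk sampling. The conflict does not remove the problem, because women can have weaned by 3 months too.

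**The case against.** **The bias may be small.** Women must intend to breastfeed to be enrolled, so most may still be giving some milk at the later sample. At 95% versus 98% lactating the illustrative bias is at most -0.04 SD. Even -0.26 SD is well below what 30 per arm can detect. This stands as to size. It does not make the comparison a randomised one.

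**The direction is not established.** The Background links low breastfeeding rates in overweight women to altered prolactin and delayed lactogenesis, which would suggest lower values in retained women. Yet at 3 months Table 2 names return to work or study and early complementary feeding, which are not supply problems. This stands: a fall in the intervention mean cannot be presumed.

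**This belongs in the statistical analysis plan.** Analysis sets and labels often do, and a plan not shown here may handle them. But the between-arm claim is made in the protocol. A later plan can redefine the target, for instance as women who would lactate under either arm, but that is a different hypothesis and rests on untestable assumptions. It cannot make the missing concentrations exist.

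**The convenience subsample already weakens the comparison.** True, but that is a separate threat. A random draw would still lose weaned women unequally if counselling works.

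**Stronger readings that the documents do not support.**
- A reader might infer that milk volume suffers in the same way. It need not: intake is estimated from recorded feeding data, zero feeds gives 0 ml, and no section excludes weaned dyads.
- A reader might infer that serum prolactin is affected. It can be measured in any woman, and nothing says weaned women are dropped.
- A reader might apply 22.8% and 45.8% to the 30 per arm to count milk samples. Those are EBF rates, and women who breastfeed partially can also give milk.

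**Conclusion.** The point holds for two outcomes, breast milk prolactin and breast milk macronutrient content, and chiefly at the later sample. For these, the stated contrast with standard management is conditional on a post-randomisation state that the trial expects to change. Neither intention to treat nor a later analysis plan can restore randomisation to it.

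Its size cannot be fixed from the document. About -0.02 to -0.26 SD is an illustration that depends on assumed rates of any breastfeeding, no true effect, and assumed lower values in retained women; the sign follows from the last assumption. The documents do not show that the trial's conclusion on milk would be reversed. They do show that a causal conclusion would lack support. Because the outcomes are secondary and measured in a subsample, the change should be made, but the primary comparisons are untouched.

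**What to change.** 1. Restate the later milk prolactin and macronutrient results as descriptive, among women still lactating. Show the number lactating in each arm beside them, and make no causal between-arm claim.
2. Give more weight to the 1-month milk sample. Selection is likely smaller there, though not nil, so the number lactating per arm should be shown at that time as well.
3. State that estimated milk intake is analysed in all randomised dyads with follow-up, scored 0 ml when the infant is no longer breastfed. This keeps the volume hypothesis a comparison of the randomised arms, apart from loss to follow-up.
4. Reconcile the later sampling time between Table 1 (3 months) and the Secondary outcomes, Data collection and Measures sections (4 months).

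The cost is outcome wording and one scoring rule, with no added visits or samples. The price is a weaker secondary claim on milk composition, and therefore on the link from milk to infant growth.
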